### Procedure

The study was approved by The Ohio State University’s Social and Behavioral Institutional Review Board (2021B0434) and the study procedures is registered on clinicaltrials.gov (trial number NCT05554198). Any changes made in the study protocol will be submitted to The Ohio State University’s Institutional Review Board for approval and updated on clinicaltrials.gov.

Once participants have been screened and are eligible, a study team member will contact the participant for an enrollment meeting. The enrollment meeting will take approximately 15 minutes to complete and take place over the phone. The enrollment meeting is comprised of the study team member educating the participant on the study, obtaining verbal consent, verifying participant contact information, and providing an overview of the Attend Behavior intervention. The participant will be emailed a link to the baseline survey after the phone call is complete. In addition to the email with the baseline (T1) survey link, the participant will be emailed a welcome email with a link to the Attend Behavior website which houses a short video created by Attend Behavior explaining the features of the program and how to use the program and a bullet pointed overview of the study. The welcome email will contain copies of the consent form and a contact card for the study team. Once the T1 survey is completed, the participant will be emailed their access code to create their Attend Behavior account. This access code allows participants to use Attend Behavior for free for up to 1 full year.

The enrollment meeting will also include assessing the participant’s preference for email, text messages, and/or Attend Behavior messaging reminders to complete the T2 survey and exit interview. Participants will be offered to schedule the exit interview during the enrollment appointment or an option to schedule the interview at a later time. Participants will be reminded that they can Zoom into the 1:1 interview or complete the interview via phone. Participants will be informed that they will receive a survey link after completing the intervention to complete approximately 12-weeks after initiating the intervention. They will be informed that the Attend Behavior mobile application will be sending them reminders to complete learning modules weekly and to practice skills taught in the modules.

## Data collection and storage

### Quantitative data

Participant including the demographic questionnaire, baseline survey (T1), and the post-intervention survey (T2) will be collected using REDCap (Research Electronic Data Capture) and stored on a secured server [43]. Data from participants’ usage of the Attend Behavior app, will be collected and stored on Attend Behavior’s servers. Encryption used by REDCap to protect respondents includes hashed passwords and SSL certificates between client and server using the secure HTTPS protocol. Data will be downloaded from both servers for cleaning, merging, and analysis using R [60]. There will be no hard copies of data in this study. All data (e.g., audio recordings, surveys) will be housed in the Ohio State University College of Nursing’s R-drive. The R-drive runs Windows Server 2012R2 and is only used to host research files. Electronic access to the research server is restricted to the college LAN or VPN. Only the study team members approved by the Ohio State University Institutional Review board will have access to the project and data on REDCap and the R-drive. Due to the small scale, short duration, and low risks of this study, a data monitoring committee was not deemed to be needed.

We will conduct exploratory data analyses to check data accuracy, examine variable distributions, and summarize sample characteristics. Data anomalies once identified will be fully investigated and remedial strategies will be considered as appropriate. Continuous data that are not normally distributed will be examined for potential outliers and data transformation will be conducted if necessary. Missing data will be examined to determine which mechanism of missingness is most likely, and if appropriate, multiple imputations will be conducted.

### Quantitative analysis plan

To address research question one, *is Attend Behavior a feasible and acceptable intervention for rural parents/guardians of children with ASD*, we will use descriptive statistics of the participant responses to the AIM, IAM, and FIM taken post intervention (T2). Specifically, we will use the mean score across all participants on the AIM to examine acceptability and the mean score across all participants on the FIM to assess feasibility of the intervention. Further, we will report the percent of individuals scoring at or above the benchmark score of 16. Additionally, we will examine the appropriateness of the intervention using the scores from the IAM in a similar manner as the AIM and FIM. Finally, we will report rates of completion of intervention, recruitment, and retention rates. To assess retention, user data from the program will be extracted to examine module completion and program engagement. This will be an exploratory measure as there is limited research on digital engagement for self-administered PT programs for parents of children with ASD. A review of studies examining parent engagement in interventions for underrepresented parents of children with social, emotional, and behavioral disorders showed an average attrition rate of 26% [61]. There was less parent attrition in intervention groups when the interventions were community/home-based, [61] therefore the goal for retention rate is 75%.

To address research question 2, *to what extent does Attend Behavior effect parental mental health (depression and stress) and child outcomes (disruptive behaviors and noncompliance in the home)*, we will summarize pre and post intervention scores using descriptive statistics to and assess change using linear regression. Specifically, we will report descriptive statistics (mean, standard deviation, median, and inn quartile range) for each outcome variable (i.e. ABC-I, HSQ-ASD, PROMIS, and PSI-SF) at preintervention (T1) and post-intervention (T2).

To assess change in outcomes will examine data from all participants who initiated the Attend Behavior modules regardless of how many they complete. To determine if those participants hand a significant change in any of the outcome measures (ABC-I, HSQ-ASD, PROMIS, and PSI-SF), we will employ a residualized change approach where each participants’ outcome measure taken at T2 is regressed on the participants’ baseline (T1) score on the same measure. These regressions will be unadjusted, meaning we will include no covariates in these analyses, as our primary interest is to determine if any intervention effect is present in the data. We will report mean differences, standard errors, 95% confidence intervals, and effect sizes for baseline (T1) to post-intervention (T2) difference. Supplementary analysis will include reexamining these models controlling for number of modules completed to determine if a certain number of models is associated with a larger effect size difference at outcome.

Of note, although the full ABC measurement will be included in the T1 and T2 surveys, only the ABC-Irritability subscale (ABC-I) will be used for assessing outcomes analyses as the intervention does not target the other symptoms included in the other ABC subscales. Other ABC subscales may be used supplementary exploratory analysis, but are not the primary focus of this study.

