## Materials and methods

### Design

This pilot study is a single group pre/post-intervention design. A mixed-methods approach will be employed with both quantitative and qualitative data analyzed. Quantitative data are collected via surveys using REDCap (Research Electronic Data Capture) [43]. Qualitative data are collected via brief 1:1 semi-structured interviews.

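### The unadjusted T2-on-T1 regression named as the test of significant change does not test mean change in a single group; the paired T2 minus T1 difference should be named instead

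*Protocol article*

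**What the plan says.** The Design section states: "This pilot study is a single group pre/post-intervention design". For research question 2, the Quantitative analysis plan says "we will summarize pre and post intervention scores using descriptive statistics to and assess change using linear regression".

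The same section then names the model. To find out whether participants "hand a significant change in any of the outcome measures (ABC-I, HSQ-ASD, PROMIS, and PSI-SF), we will employ a residualized change approach" (the first word is evidently a misprint for had), each "outcome measure taken at T2 is regressed on the participants’ baseline (T1) score on the same measure". It adds: "These regressions will be unadjusted, meaning we will include no covariates in these analyses". The reason given is that "our primary interest is to determine if any intervention effect is present in the data".

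The next sentence promises further output: "We will report mean differences, standard errors, 95% confidence intervals, and effect sizes for baseline (T1) to post-intervention (T2) difference". A supplementary analysis refits the models with the number of completed modules added.

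**The concern.** Residualized change is a way to compare groups, or to test a predictor, after removing the part of T2 that T1 explains. The main model here has no group, no time term and no predictor other than T1, so nothing is left for the residualized score to be compared on. Yet this model is given the task of deciding whether change, and even an intervention effect, is present.

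At stake is how the secondary aim is reported on four outcomes (ABC-I, HSQ-ASD, PROMIS Depression and PSI-SF), which the Purpose section says will influence later randomized trials. An analyst who follows the stated model and reads its printed p-values could report change where there is none, or miss change that occurred. The separately promised mean difference could disagree with that reading, and the text does not say which governs.

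**Working it through.** **Inputs from the article.** One group; model T2 = a + b × T1 + error; enrolment target 40 (Participants); retention goal 75% (Quantitative analysis plan), so 40 × 0.75 = 30 with both scores. The article gives no mean, SD, T1–T2 correlation or alpha, and no figure of its own to reproduce.

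**Step 1: algebra, with no assumed figures.** Write x for T1 and y for T2. Least squares gives b = Sxy / Sxx and a = ȳ − b·x̄. Add the same constant c to every T2 score:

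- Sxy, Sxx and b are unchanged. So are every residual, the residual variance, the slope's standard error and p-value, and R².
- The residuals average zero before and after the shift.
- Only the intercept moves, from a to a + c. Its default test asks whether predicted T2 at T1 = 0 is zero, not whether c is zero.

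Mean change equals ȳ − x̄ = a + (b − 1)·x̄. It combines both coefficients with the baseline mean, and no single default coefficient equals it. With equal means and SDs and no change, the expected intercept is mean × (1 − r): for a mean of 50 and r = 0.5, 50 × 0.5 = 25.

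**Step 2: one simulated data set** (n = 30, mean 50, SD 10, correlation 0.5), with T2 shifted:

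| Shift in T2 | Slope | Slope p | R² | Paired difference | Paired p |
|---|---|---|---|---|---|
| 0 | 0.350 | 0.055 | 0.125 | 0.06 | 0.97 |
| −5 | 0.350 | 0.055 | 0.125 | −4.94 | 0.008 |
| −10 | 0.350 | 0.055 | 0.125 | −9.94 | < 0.0001 |

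**Step 3: rejection rates over 5,000 simulated trials.** Assumed: bivariate normal, n = 30, mean 50, SD 10 at both times, two-sided 0.05.

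| Correlation | True change | Slope = 0 | Intercept = 0 | Centred intercept, default SE | Paired |
|---|---|---|---|---|---|
| 0.3 | none | 38% | 94% | 10% | 5.0% |
| 0.5 | none | 83% | 81% | 9% | 4.9% |
| 0.7 | none | 99.6% | 57% | 7% | 4.6% |
| 0.3 | −0.5 SD | 37% | 87% | 75% | 61% |
| 0.5 | −0.5 SD | 83% | 64% | 84% | 77% |
| 0.7 | −0.5 SD | 99.6% | 30% | 94% | 93% |

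Apart from simulation error, the slope test gives the same rate with and without change. The intercept test rejects less often when scores really fall. Adding mean/SD of 18/8 and 55/9 widens the no-change ranges a little: slope about 37% to over 99%, intercept about 95% down to 51%, centred intercept about 12% down to 6%, paired about 5%.

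**Step 4: why the mean-centred version is not a full repair.** Regressing T2 − T1 on mean-centred T1 gives an intercept equal to the mean change. Its default variance, however, is about σ²(1 − r²)/n, because it treats the sample baseline mean as fixed. The variance of the paired mean difference is 2σ²(1 − r)/n. The ratio is (1 + r)/2, which is 0.65, 0.75 and 0.85 at r = 0.3, 0.5 and 0.7. The default standard error is therefore too small by a factor of 0.81, 0.87 and 0.92, which accounts for the 10%, 9% and 7% in the table.

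**The case against.** The strongest reply is that the article already promises the right quantity. A 95% interval for the mean T1-to-T2 difference, computed as a paired difference, is equivalent to a two-sided 5% test of change. Research question 2 asks to what extent outcomes change, which is a question of estimation. T1 and T2 summaries are planned as well. This stands. A reader might infer that the question will be answered only by a statistic without information about change, and so wrongly on all four outcomes; the documents do not support that.

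Second, the article never says which coefficient or p-value would be read as evidence of change. This also stands. A reader might take the slope's rejection rate as the plan's false-positive rate, but that presumes a test the text does not name, and the rate depends heavily on the assumed correlation. Nor is the fitted model wholly uninformative: the intercept moves one-for-one with a uniform shift, and the centred form targets mean change with only mild inflation.

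Third, this is the secondary aim of a pilot that claims no power, and an article may leave computing details to a fuller plan. The feasibility and acceptability analysis is indeed untouched. But the article does not leave the model open: it states both the model and its purpose, and the two do not match. It assigns the finding of significant change to the regression, not to the interval, and gives no route from one to the other.

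A reader might also connect the general data-checking provision that "data transformation will be conducted if necessary" (Quantitative data). That is conditional, a separate matter, and no part of this mismatch.

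**Conclusion.** The point holds as a mismatch between a stated model and its stated purpose. By algebra alone, the slope test cannot detect a uniform change and the uncentred intercept test asks a different question. The promised mean difference limits the harm, provided it is computed as a paired difference and allowed to govern; the text secures neither. The rejection rates in the tables illustrate what would follow from reading default coefficient tests as tests of change. They rest on assumed means, SDs, correlations, normality, 30 completers and a two-sided 0.05 level, and they are not error rates of the plan itself. The correction should be made before analysis. Even the corrected analysis estimates change, not an effect attributable to the intervention, because there is no comparator; that is a separate limitation.

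**What to change.** For each of the four outcomes, name the mean within-person difference (T2 minus T1) as the change analysis, with its paired standard error, 95% confidence interval and a defined standardized effect, for example mean change divided by the baseline SD. State that this interval is the basis for any statement about change.

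Keep the regression of T2 on T1 for the supplementary modules-completed question, where there is a predictor to test. Do not obtain the mean change from a mean-centred intercept with its default standard error.

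A two-occasion mixed model with time as fixed effect is an alternative that also uses T1 from participants without T2. It matches the paired analysis only when data are complete, so if it is chosen it should be named as such.

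The cost is a change of wording in the protocol or analysis plan. No new data, visits or participants are needed.

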### Qualitative data and analysis

Qualitative data sources in this study include the exit interview completed at the end of the 12-week intervention. Participants and a study team member will complete the 1:1 semi-guided interview via Zoom or phone. Interviews will take approximately 20–30 minutes. Participants will be given the interview guide questions in advance. Interviews will be audio recorded. All audio files will be transcribed verbatim promptly after the interviews. A member of the study team will review the transcripts of the audio interviews for accuracy. Prior to data analysis, all qualitative sources will be de-identified with identifiers being redacted. All qualitative data will be analyzed using NVIVO.

NVIVO will assist with the organization and coding of the unstructured narrative data. NVIVO has several capabilities including classifying and arranging data and organizing the data into similar concepts to allows for relationships to emerge. The PI and a member of the research team will read all participant interviews. Codes and coding categories will be compared and discrepancies discussed before establishing a codebook.

Due to the qualitative methodology chosen, data analysis will occur simultaneously with data collection. Data saturation will be attained when no new additional data are revealed in the conceptual categories. The data analysis strategy that will be used in the proposed study is content analysis due to the inductive nature of the work. The goal of the content analysis is to offer a detailed depiction of the phenomena of interest using the participant’s own words. The researcher avoids making inferences and instead stays closely aligned with the data by frequently using quotes, nothing themes or codes, and the frequency of the codes. To ensure credibility of the data, the PI will keep a “reflective commentary” log to acknowledge biases and note initial impressions as well as themes as they emerge in the data.

## Monitoring adverse events

Study monitoring and detection of any adverse events will take continuously throughout the study. There are minimal risks associated with this study and include fatigue and time involvement. All videos, prompts, and interview questions are not beyond what is ordinarily encountered in daily life or during the performance of routine psychological tests. Participants are given contact information and encouraged to reach out anytime to the study primary investigatory and/or the institution’s Office of Responsible Research Practices.

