### Participants

We aim to enroll 40 participants. Due to this study’s pilot nature, we will not rely on statistical power for analysis. A sample of 40 participants will likely be met the guideline of 12 or more participants for pilot studies using continuous variables even accounting for potentially high participant attrition [44].

Participants will be recruited with the aid from various agencies and organizations with advertisement of the study within the Untied States. Study team members will reach out to rural community-based mental health agencies, schools, libraries, Boards of Developmental Disabilities, and other agencies that are likely to have close contact with families of children with ASD. If the agency or organization is interested, they will be given flyers to disperse to families as they see fit and/or hang in their building(s). In addition, we will partner with The Ohio State University Extension Offices in rural counties to advertise the study. Finally, Facebook will be used for recruitment by both Facebook ads and sending study information to Facebook groups that are specific to parents of children with ASD. Recruitment to the study opened in January 15, 2023 and is anticipated to close by April 2024. See Fig 1 for the SPIRIT schedule of enrollment, interventions, and assessments and Fig 2 for the study timeline.

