### The acceptability of intervention (AIM), intervention appropriateness measure (IAM), and the feasibility of intervention measure (FIM)

The AIM, IAM, and FIM have a total of 12-items answered on a Likert scale of 1 = *completely disagree* to 5 = *completely agree*. The AIM, IAM, and FIM is a brief and reliable measurement to examine implementation success [58, 59]. Higher overall scores correlate with higher rates of participant perceptions of intervention acceptability, appropriateness, and feasibility. Since scores of 4 and 5 indicate that participant agrees or completely agrees, scores of ≥16 for each scale will be used as benchmarks for acceptable, appropriate, and feasible outcomes. Although there is no set cut-off score available for the AIM, IAM, and FIM, the score of ≥16 is chosen because item scores of 4 and 5 suggest that the respondent agrees or completely agrees that Attend Behavior is acceptable, appropriate, or feasible.

The demographic survey and ASRS-SF will only be given at T1. The ABC, HSQ-ASD, PROMIS Depression 6a, and the PSI-SF will be delivered at both T1 and T2. The AIM, IAM, and FIM will only be delivered at T2.

After the T2 survey is complete, participants will be invited to complete an approximately 20-minute exit interview with the PI. The exit interview will be conducted over the phone or zoom according to participant preference. The purpose of the post-intervention interview is to gauge the preliminary feasibility and acceptability of Attend Behavior. The interview will be guided by a semi-structured interview guide. Interviews will be audio-recorded and transcribed. Examples of questions that will be asked during the 1:1 exit interviews include “What did you learn from the program,” “What did you like least about the program,” and “What is the online parenting program missing that could help parents like you who have a child with autism in rural areas?”

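### Adverse-event detection is described as continuous, but the only route described is participants getting in touch, so events may be under-counted and a zero count would not show absence of harm

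*Protocol article*

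**What the plan says.** All references are to the protocol article.

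- *Monitoring adverse events* makes a positive statement about ascertainment: "Study monitoring and detection of any adverse events will take continuously throughout the study". The mechanism it gives is "Participants are given contact information and encouraged to reach out anytime to the study primary investigatory and/or the institution’s Office of Responsible Research Practices". It describes the risk as low: "There are minimal risks associated with this study and include fatigue and time involvement".
- *Procedure* describes an enrolment call before access is given, emails, reminders about the T2 survey and exit interview, and app reminders about modules and skill practice. It describes no check-in about problems during the 12 weeks.
- The section on the AIM, IAM and FIM sets out survey timing: "The ABC, HSQ-ASD, PROMIS Depression 6a, and the PSI-SF will be delivered at both T1 and T2", with the AIM, IAM and FIM added at T2. None of these is described as collecting adverse events. The exit interview is by invitation after T2, and its stated purpose is feasibility and acceptability.
- *Quantitative data* adds that "a data monitoring committee was not deemed to be needed".
- *Participants* gives the sample size: "We aim to enroll 40 participants". *Quantitative analysis plan* sets the target for staying in the study: "therefore the goal for retention rate is 75" percent.

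**The concern.** The section promises detection, and detection of any event. The method described is spontaneous reporting, which records only what a parent decides to raise. An open channel is available all the time, but it does not find events by itself.

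The difference has some substance here. The program is used at home without a clinician, its course list includes planned ignoring and time out, and the article says that no published study has examined its effects in parents of children with ASD. Worsening of behavior or of parental distress is a foreseeable event that a parent may not think to report to a research team. The pilot is meant to inform a larger randomized trial. If its report says that few or no events occurred under continuous monitoring, readers may give that count more weight than the method supports.

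**Working it through.** **Text side by side.** The article states no adverse-event rate, count or detection probability, so there is no figure to reproduce. The main check is whether any other section supplies an active route.

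| Possible route | What the article describes | Identifies individual events? |
|---|---|---|
| Contact during the 12 weeks | Reminders about modules, T2 and the interview | No |
| T2 survey | ABC, HSQ-ASD, PROMIS Depression, PSI-SF, AIM, IAM, FIM | Not as planned |
| Exit interview | Voluntary; feasibility and acceptability; example questions only | Possibly, incidentally |
| App usage data | Module completion and engagement | No review for harms described |

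The T2 scales come closest. They are analysed as group summaries and regressions, and no rule turns one participant's worsening into an event. Their windows are also short: four weeks for the ABC and HSQ-ASD, seven days for PROMIS Depression. With T2 at about 12 weeks, the four-week window leaves about 12 − 4 = 8 weeks uncovered, so worsening that resolves earlier is not seen. Those who do not complete T2 are not seen at all.

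**Illustration of size.** Inputs from the article: n = 40 enrolled; 75% retention goal, so 40 × 0.75 = 30. Assumptions, none of them in the article: true per-participant event rate p of 5% or 10%; share of events volunteered s; independent participants; complete answers to a direct question; and 30 T2 respondents with the same event rate as the rest. The article assesses retention partly through module use, so treating 75% as the T2 response is itself an assumption.

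Chance that no event is recorded = (1 − p × s)^n.

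| Situation | p = 10% | p = 5% |
|---|---|---|
| Volunteered only, s = 0.25, n = 40 | 0.975^40 = 36.3% | 0.9875^40 = 60.5% |
| Volunteered only, s = 0.50, n = 40 | 0.95^40 = 12.9% | 0.975^40 = 36.3% |
| Volunteered only, s = 0.75, n = 40 | 0.925^40 = 4.4% | 0.9625^40 = 21.7% |
| Direct question only, n = 30 | 0.90^30 = 4.2% | 0.95^30 = 21.5% |
| Full ascertainment, n = 40 | 0.90^40 = 1.5% | 0.95^40 = 12.9% |

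The gain from a direct question thus depends on s. It is large if a quarter or half of events would be volunteered. If three quarters would be, a direct question put to 30 does about as well as volunteering among 40, and the benefit lies in having both routes.

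**What a zero count would exclude.** The one-sided 95% upper bound for 0 events in n is 1 − 0.05^(1/n). This is 7.2% for n = 40 and 9.5% for n = 30. If only half of events were volunteered, the bound from 0 of 40 becomes 7.2% / 0.50 = 14.4%; at a quarter it is 28.9%.

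**The case against.** The strongest reply is that this is a condensed article. Event forms and the complete interview guide may sit in the full protocol approved by the institutional review board, and the article gives only examples of interview questions. One of them asks what participants liked least, which may bring out some harms. This stands, and the absence of such detail is not the point made here. What remains is that a section devoted to monitoring claims continuous detection and names a method that does not provide it.

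A second reply is that a channel open at any time is continuous. That is fair for monitoring in the sense of availability, but it does not amount to detection of any event.

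A third is that the ABC, HSQ-ASD, PROMIS Depression and PSI-SF already ask about the most plausible harms, so parents need not volunteer them. This is largely right for T2 completers. A reader might infer that harms go unmeasured, and the article does not support that. The limits are the short look-back, the group-level analysis and the loss of non-completers.

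A fourth is that nothing rests on event counts. Feasibility and acceptability are judged on the AIM, FIM and IAM, completion, recruitment, retention and interviews. This also stands. A reader might infer that the pilot will use a zero count to claim safety or to decide on the larger trial; the article says neither.

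Finally, a single question at about 12 weeks is not continuous detection either, and it misses dropouts. Both are true, which is why the wording needs to change as well.

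**Conclusion.** The mismatch holds, in a limited form. Continuous detection is claimed, participant-initiated contact is what is described, and no listed T2 instrument is described as asking about adverse events. Events may be under-counted, so a low or zero count would be weak evidence of absence of harm.

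It would be tempting to say that harms will be under-counted. The article does not support that certainty, because it gives no event rate and no reporting rate. The 13% against about 4% comparison rests on an assumed 10% event rate, half of events volunteered, and 30 complete answers to a direct question. At an assumed 5% rate the same comparison is 36.3% against 21.5%. Under other assumed shares the gap can be wider or can vanish.

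The consequence is modest, since the study is described as minimal risk and no endpoint or decision depends on event counts. Minor priority.

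**What to change.** 1. Add one structured question to the T2 survey on any unwanted effect or worsening, for parent or child, since starting the program. Add it to the exit interview guide too if it is not already there.
2. Tabulate solicited and volunteered events separately, giving the number who answered the question as the denominator for the former.
3. Reword *Monitoring adverse events* to say that reporting between scheduled contacts is participant-initiated and that a zero count will not be read as evidence of safety.

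The cost is one survey item, possibly one interview question and a minor amendment for the institutional review board. The reported event count may rise. Dropouts would still be missed by the new question, and participants already past T2 would be covered only by the rewording. Recruitment opened in January 2023 and was expected to close by April 2024, so the rewording may be the only part that applies to everyone.
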